##### Evaluation criteria

- - 1. Definitions
- *baseline" values* for heart rate (HRbl) and systolic blood pressure (SBPbl) are the mean of 3 measurements taken before the start of anesthesia
- *hemodynamic reactivity*: HR > 120% of HRbl or SBP > 120% of SBPbl
- *hypotension*: PAS <75 mmHg
- *bradycardia*: HR < 40 min-1
- *intervention*: begins with skin preparation, includes surgery and ends with the end of dressing
  - 1. main criterion, making it possible to meet the main objective

Total quantity of remi administered (value related to weight and duration of intervention).

- - 1. secondary criteria to meet secondary objectives:

NB: several criteria are assessed after the patient wakes up, between extubation (H0) and H2 120 min after extubation. The patient does not need to be in the intensive care unit for this assessment; he/she can be in his/her hospital room.

- Proportion of time spent in hemodynamic reactivity, hypotension or bradycardia during the procedure. This proportion will be equal to the cumulative duration of each episode of reactivity, hypotension or bradycardia, divided by the duration of the procedure Total dose of Ephedrine.
- ANIi and ANIm: proportion of time spent during the intervention in the following intervals :

<50, [50-70], >70

- hypnotic component measurement index (BIS® or Entropie®): proportion of time spent during the procedure in the following intervals: <40, [40-60], >60
- ANI, heart rate, blood pressure, FetCO2, Pmax (ventilator) 5 min before start of procedure, 5 min after start of procedure and 20 min after start of procedure.
- Pain assessed by visual analog scale (VAS) between H0 and H2, every 15 min.
- Total quantity of morphine administered between end of surgery and H2 post-op.
- Total quantity of ketamine administered between end of surgery and H2 post-op.
- Frequency of postoperative nausea/vomiting assessed at H2.
- Number of changes in remifentanil flow rate during the procedure.
- Total quantity of propofol administered (absolute value, value related to weight, value related to weight and duration of procedure).
- Number of propofol target changes during the procedure.

In the *"ANI-loop"* arm only: number and total duration of disengagements of the ANI-loop device during the operation, i.e. the number of times and cumulative duration that the closed-loop system had to be interrupted and replaced by manual control, as in the standard practical arm.

##### Calculating the number of subjects

The aim of the study was to assess whether the ANI-loop medical device could reduce the total amount of remifentanil (remi) administered compared with standard practice. Based on literature data [Leal PC et al.] and the department's usual practice, the total amount of remifentanil in the control group can be estimated at 0.30 ± 0.075 (mean ± standard deviation). To demonstrate a 20% reduction in the *ANI-loop* arm (i.e., a mean remifentanil quantity of 0.24 in the experimental group), with a first-species risk of 5% and a power of 80%, we need to include 26 patients per group, for a total of 52 patients.

Reference:Leal PC, Sakata RK, Salomão R, Sadatsune EJ, Issy AM. Braz J Anesthesiol. 2013 Mar- Apr;63(2):178-82.

##### Analysis method and strategy

Statistical analyses will be carried out using SAS software (version 9.4 or higher) at the Lille CHRU's methodological support platform, under the responsibility of [name]. All statistical tests will be two-sided, with a first-species risk of 5%. No intermediate analyses are planned. A detailed statistical analysis plan will be drawn up and validated before the database is frozen.

Patient characteristics at inclusion will be described for each of the two study arms. Qualitative variables will be described by numbers and percentages. Quantitative variables will be described by the mean and standard deviation in the case of a Gaussian distribution, or by the median and interquartile range (i.e. 25th and 75th percentiles) in the opposite case. The normality of distributions will be tested by a Shapiro-Wilk test and verified graphically by histograms.

Primary objective: The total amount of remifentanil administered (value related to weight and duration of intervention) will be compared between the two arms of the study by a Student's t-test; the effect size will be calculated (standardized mean difference) with a 95% confidence interval. If the distribution of the primary endpoint deviates from normality, the Mann-Whitney U test will be used.

Secondary objectives: Qualitative secondary endpoints will be compared between the two arms of the study using a Chi-square test or Fisher's exact test (when the validity conditions of the Chi-square test are not met). Quantitative secondary endpoints are compared between the two arms of the study using a Student's t-test, or a Mann-Whitney U-test if the distribution of the endpoint deviates from normality. Quantitative secondary endpoints measured at different times will be compared between the two arms of the study using a linear mixed model. This model takes into account the correlation between repeated measurements in the same patient, and the possible existence of missing data. The choice of correlation model will be based on the AIC criterion. The validity of the model will be studied by analyzing the residuals. In the event of significant deviations from normality without obvious transformation of the criterion, the criteria will be compared at each time point between the groups using Mann-Whitney U tests. Finally, secondary criteria identified only in the

The "*ANI-loop*" model will be described using the usual descriptive statistics.

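### A normality check picks the primary test and only a standardized difference is named, so the 20% mean reduction that sized the trial is not the named primary estimate

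*Protocol*

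**What the plan says.** The main objective (Protocol 3.1) is whether the device lowers the amount of remifentanil given. Section 4.4 turns this into a difference in means. It takes 0.30 with SD 0.075 in the control arm and a 20% reduction, "i.e., a mean remifentanil quantity of 0.24 in the experimental group", and concludes: "with a first-species risk of 5% and a power of 80%, we need to include 26 patients per group, for a total of 52 patients".

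Section 4.5 compares the endpoint by Student's t-test and states that "the effect size will be calculated (standardized mean difference) with a 95% confidence interval". It then says: "If the distribution of the primary endpoint deviates from normality, the Mann-Whitney U test will be used". The synopsis repeats both. Section 4.5 also says that normality is examined by Shapiro-Wilk and by histograms. It gives no significance level and does not say whether the check applies to each arm, to the pooled data or to residuals. It names no raw difference, ratio or percentage reduction, and no estimate to accompany Mann-Whitney. It announces a detailed statistical analysis plan before the database is frozen.

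**The concern.** There are two mismatches between the question and the analysis.

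- **Effect measure.** The trial is sized on a percentage fall in the mean, but the named result is in SD units. The same SMD corresponds to different percentage reductions depending on the spread, so it does not by itself tell the reader whether the target was reached.
- **Test.** The data decide which hypothesis is tested. Student's t concerns means. Mann-Whitney concerns whether values in one arm tend to be lower than in the other, and with unequal, skewed spreads it can reject when the means are equal. On that branch the primary result has a p-value but no matching estimate or interval.

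This matters because a rank-test rejection could be presented as evidence of a lower mean amount, and the headline figure would not be the quantity the trial was designed to estimate.

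**Working it through.** **1. The plan's own figure.** Inputs from section 4.4: means 0.30 and 0.24, SD 0.075, power 80%. Section 4.5 gives two-sided 5%. By normal approximation, n per group = 2 × (1.960 + 0.842)² × (0.075/0.06)² = 2 × 7.85 × 1.5625 = 24.5, so 25. The exact noncentral t gives 25.52, so 26, with power 80.7%. The stated 26 per group is reproduced.

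**2. What the SMD conveys.** Design SMD = 0.06/0.075 = 0.80. Percentage reduction implied by an SMD of 0.8 = 100 × 0.8 × SD/0.30. SDs other than 0.075 are assumed:

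| SD | Reduction implied by SMD 0.8 |
|---|---|
| 0.05 | 13% |
| 0.075 | 20% |
| 0.10 | 27% |
| 0.15 | 40% |

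For data that fall exactly on the design values:

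- SMD: 0.80, 95% CI about 0.24 to 1.36.
- Mean difference: SE = 0.075 × √(2/26) = 0.0208. With t(50) = 2.009, the CI is 0.06 ± 0.042, or 0.018 to 0.102. That is 6% to 34% of 0.30 with the control mean taken as fixed.
- Ratio of means: SE of the log ratio = (0.075/√26) × √(1/0.30² + 1/0.24²) = 0.0147 × 5.336 = 0.0785. Then exp(ln 0.80 ± 2.009 × 0.0785) = 0.683 to 0.937, a reduction of 20% (95% CI about 6% to 32%).

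The last two answer the question in section 4.4. Neither is named.

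**3. How often the test would switch.** Assume Shapiro-Wilk at 5% in each arm, switching if either arm rejects, with 26 per arm. For normal data the expected rate is 1 - 0.95² = 9.75%, and simulation gives about 10%. With lognormal data it is 41-42% at CV 25% (the CV implied by 0.075/0.30) and about 85% at CV 50%.

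**4. Rejection rate when both arms share one distribution.** In 20,000 simulated trials per case, the two-step rule rejects in 4.7% to 5.4% across normal, lognormal, exponential, heavy-tailed t and uniform data. This holds whether normality is checked per arm, pooled or on residuals.

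**5. Rejection rate with equal means but different spreads.** All spreads are assumed, because the documents give no SD for the ANI-loop arm. A lognormal has median = mean/√(1 + CV²), so the ratio of medians is √(1.0625)/√(1 + CV²).

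| Arms, equal means | Ratio of medians | Two-step rule | Fixed t-test |
|---|---|---|---|
| Normal, SD 0.075 vs 0.15 | 1.00 | 4.7-5.9% | Welch 4.7%, Student 4.9% |
| Lognormal, CV 25% vs 40% | 0.957 | about 8% | not tabulated |
| Lognormal, CV 25% vs 50% | 0.922 | about 12% | Welch 5.8% |
| Lognormal, CV 25% vs 60% | 0.884 | about 17% | Welch 6.1%, Student 6.3% |

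In the last row Mann-Whitney used alone rejects in about 17%, the same as the two-step rule. The excess therefore comes from the rank test responding to a real difference in distributions, here medians about 12% apart with equal means. It does not come from the preliminary check.

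**6. Cost in power.** At the design values, simulated power is 80.6% for Welch and 80.6% for the two-step rule.

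**The case against.** The best defence has four parts.

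- **Error rate.** A reader might infer that pre-testing for normality inflates the type I error. Step 4 does not support that. The excess in step 5 needs equal means, skewed data and clearly different spreads together, and it is error only against an equal-means null. Smaller contrasts do little: 6.2% at CV 25% vs 30% and 6.6% at 25% vs 35%. Appendix I limits the automatic rate to 0.05-0.6 µg/kg/min. If 0.30 is in that unit (section 4.4 gives none), a lognormal with CV 60% would put about 6% of patients above the limit, so the most extreme case fits the device arm poorly. All of this stands.
- **Estimability.** A reader might infer that the 20% reduction could never be estimated. That is too strong. On the t-test branch, arm means and SDs would yield the raw and percentage difference. Nothing says the SMD is the sole measure, or withdraws it after a switch. One caution remains: section 4.5 describes non-Gaussian variables by median and interquartile range. If that convention were carried to the endpoint, the arm means might not be shown.
- **Student's test.** A reader might also fault the pooled variance. With equal arms of 26 it differs from Welch by about 0.2 points in the cases tabulated, so this is immaterial.
- **The later analysis plan.** It may add a raw difference and define the check. But the effect measure and the switching rule are positive choices in the protocol, not gaps left open, and a plan that follows the protocol inherits them.

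The switching rates also assume a mechanical 5% test, whereas the protocol adds a look at histograms. The true rates are therefore unknown.

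**Conclusion.** The point holds as a mismatch between objective and analysis. The primary test depends on a loosely defined normality check, and the only named effect measure is not the percentage reduction in the mean that sized the trial. After a switch the test no longer concerns that mean and has no matching estimate.

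The frequency of switching (about 10% with normal data, 41-42% with lognormal CV 25%) rests on an assumed 5% Shapiro-Wilk test per arm. The documents do not support a general claim of inflated error. Rates of about 8% to 17% arise only under assumed unequal, skewed spreads and reflect what Mann-Whitney tests. The sample size is correct and unaffected. This should be corrected, but it does not undermine the design.

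**What to change.** In section 4.5 and the synopsis, prespecify one primary analysis whatever the normality check shows:

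- a two-sided Welch t-test on the mean difference in the weight- and duration-related amount, with its 95% CI;
- the percentage reduction, from the ratio of means, with its 95% CI;
- Mann-Whitney with the Hodges-Lehmann shift, and the SMD, as supportive results.

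Shapiro-Wilk and the histograms can stay as description, without deciding the primary test. The cost is a few lines of text, with no extra patients or data and no loss of power at the design values.

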- propofol target adapted in both arms to maintain the hypnotic component index (BIS® or Entropy®) in the range [40-60]. During *the procedure*, propofol target changes will be made 1 minute after the last target change has become effective, and will follow the indications in table 1. This corresponds to the usual management in the burn unit of the Burn Treatment Center.

|  |  |  |
| --- | --- | --- |
| component  hypnotic | propofol target |  |
| >80 | + 2.0 |  |
| >60 | + 1.0 |  |
| <40 | - 0.5 |  |
| <25 | - 1.0 |  |
| **Table 1: Adaptation of propofol targets in both arms** | | |

|  |  |  |
| --- | --- | --- |
| ANI | target remi |  |
| <35 | + 2.0 |  |
| <50 | + 1.0 |  |
| >70 | - 0.5 |  |
| >90 | - 1.0 |  |
| **Table 2: Adaptation of remi targets in the "standard practice" arm** | | |

- remifentanil target
  - **in the *standard practice* arm**: increased to 4 ng.ml-1 at the start of *the procedure*, then adjusted to maintain ANI in the range [50-70] as indicated in Table 2. Target changes are made 1 minute after the last target change has become effective. This corresponds to usual management at the Burn Treatment Center.
  - **in the *ANI-loop* arm**, the automatic mode of the ANI-loop device is engaged at the start of *the procedure*. The flow of remifentanil is automatically regulated by the ANI-loop. The anaesthetist can switch to manual mode at any time in the event of inadequate regulation (device disengagement). The device is switched off at the end of the *procedure.*

Pre-emptive analgesia

- local infiltration of skin sample area with naropein 2 mg.ml-1 during

*intervention*

- paracetamol 1g IVL at end of *procedure*
- sufentanil 0.12 µg.kg-1 (max 10 µg) IVL at *end of procedure*

Prevention of postoperative nausea/vomiting

- ondansetron 4 mg IVL

Postoperative analgesia

- morphine titration according to Visual Analogue Scale (VAS), bolus of 3mg every 3 min (max 12mg)
- ketamine 20 mg IVL for persistent pain with VAS ≥ 40

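### For repeated secondary criteria, the non-normality fallback is one uncorrected test per time point with no overall comparison, and the reading taken before the device is engaged has no baseline role

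*Protocol*

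**What the plan says.** Under *Evaluation criteria*, the protocol lists two groups of repeated secondary criteria. ANI, heart rate, blood pressure, FetCO2 and Pmax are recorded "5 min before start of procedure, 5 min after start of procedure and 20 min after start of procedure". Pain on the visual analogue scale (VAS) is recorded "between H0 and H2, every 15 min".

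Under *Practical aspects of the research*, induction is planned to be similar in both arms, and "the automatic mode of the ANI-loop device is engaged at the start of" the procedure. The -5 min reading therefore comes before any automatic remifentanil delivery.

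Under *Analysis method and strategy*, quantitative criteria with several measurement times are compared between arms by a linear mixed model, chosen because it handles within-patient correlation and missing values. The fixed effects and the tested contrast are not named, and the -5 min reading is not called a baseline or a covariate. If residuals depart markedly from normality and no transformation is evident, "the criteria will be compared at each time point between the groups using Mann-Whitney U tests". The section also states: "All statistical tests will be two-sided, with a first-species risk of 5" per cent. It gives no correction across time points and no comparison that decides the question. It announces a detailed statistical analysis plan before database freeze.

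**The concern.** Two separate matters are involved.

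First, the fallback turns one comparison per criterion into three or nine. Nothing says which time point counts, or how a mix of significant and non-significant results is to be read. Less immediate postoperative pain is a named secondary objective, and the VAS series is the criterion with the most time points. The fallback also gives up the handling of correlation and missing data for which the mixed model was chosen. For the five intraoperative variables, one of the three tests is made before the device is running. If induction is the same in both arms as planned, a significant result there can only be chance.

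Second, the -5 min reading appears only as one more compared value. It carries information on each patient's starting level that could sharpen the comparison at +5 and +20 min. The protocol does not put it to that use.

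**Working it through.** **The plan's own figure.** The protocol gives no figure for the repeated-measures analysis. Its only calculation is for the primary endpoint: "with a first-species risk of 5% and a power of 80%, we need to include 26 patients per group". With control mean 0.30, SD 0.075 and expected mean 0.24, the standardised difference is (0.30 - 0.24)/0.075 = 0.80. Exact t-test power is 0.791 at 25 per arm and 0.807 at 26. The 26 is reproduced and is not in question.

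**Inputs.** From the protocol: 26 per arm, two-sided 5% per test, three intraoperative times, and VAS every 15 min from 0 to 120 min, which is 120/15 + 1 = 9 readings if both ends count. Not in the protocol, so assumed: the within-patient correlation (range shown) and, for power, a device effect of 0.6 SD.

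**Check 1: false positives under the fallback.** If the tests were independent, the chance of at least one p < 0.05 with no true effect is 1 - 0.95^k. For k = 3 this is 14.3%; for k = 9 it is 37.0%. Repeated readings are correlated, so the real figure is lower. Simulation of Mann-Whitney tests with no effect, 26 per arm, 40,000 runs per row:

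| Readings | Correlation pattern | 0.5 | 0.7 | 0.9 |
|---|---|---|---|---|
| 9 (pain) | equal between all times | 27% | 21% | 13% |
| 9 (pain) | decaying with time, AR(1) | 32% | 28% | 18% |
| 3 (intraoperative) | equal between all times | 12% | 11% | 8% |
| 3 (intraoperative) | decaying with time, AR(1) | 13% | 11% | 9% |

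Each single test stays near 5%; the excess belongs to the set. In the same nine-reading runs, one Mann-Whitney test on each patient's time-weighted mean rejected in 4.8% to 5.0%.

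**Check 2: role of the -5 min reading.** Take unit variance at each time, equal correlation r, an effect of 0 at -5 min and d = 0.6 at +5 and +20 min. The between-patient variance and the effect for each analysis are:

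- (a) arm effect averaged over all three times: variance (1 + 2r)/3, effect 2d/3 = 0.40
- (b) mean of the two later readings, unadjusted: variance (1 + r)/2, effect 0.60
- (c) later mean minus the -5 min reading: variance (1 + r)/2 + 1 - 2r, effect 0.60
- (d) later mean adjusted for the -5 min reading: variance (1 + r)/2 - r², effect 0.60

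Example at r = 0.6: the variances are 0.733, 0.80, 0.60 and 0.44, so the standardised effects are 0.467, 0.671, 0.775 and 0.905. Exact t power with 26 per arm (ignoring the one degree of freedom spent on the covariate):

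| r | (a) all three | (b) later only | (c) post minus pre | (d) adjusted |
|---|---|---|---|---|
| 0.3 | 49% | 75% | 54% | 81% |
| 0.5 | 41% | 69% | 69% | 85% |
| 0.6 | 38% | 66% | 78% | 89% |
| 0.7 | 35% | 63% | 89% | 94% |

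Adjustment gives the highest power at every correlation shown. Only (a) shrinks the effect, by one third.

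**The case against.** The strongest reply is that the protocol specifies very little here and leaves the rest to the announced analysis plan. A reader might infer that the mixed model averages the arms over all three times and so dilutes haemodynamic effects by a third, with power near 38%. The text does not support that. It names no contrast, and an arm-by-time or time-specific contrast fits its sentence equally well and is not diluted. Keeping the -5 min reading among the outcomes is also sound if the arm means are constrained equal at that time. This part of the objection stands, so dilution is only a possibility.

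A reader might also infer that the pain objective can be claimed from any one of nine time points. The protocol sets no such rule; it simply sets no rule at all. Nor does it give a VAS distribution. The trigger is residual non-normality that resists transformation, so whether the fallback will be used is a judgement.

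The reach is limited as well. Haemodynamic stability and time with ANI between 50 and 70 are assessed mainly by proportions of time, one value per patient, which this point does not touch. Pain has no reading before the device, so the baseline argument does not apply to it.

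What the objection does not remove is the fallback. It is a stated rule, with a stated test and a stated level, and not a detail left open.

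**Conclusion.** The point holds in a limited form. The fallback as written is a poor rule. If it is triggered for pain, it carries about a 13% to 32% chance of at least one false positive across nine readings, for assumed correlations of 0.9 to 0.5, and names no overall comparison. For the five intraoperative variables, it spends one test in three on a time when the device cannot have acted.

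The missing baseline role is a lost gain and not an error of validity. Against a post-minus-pre contrast, which is not diluted, adjustment raises power from 54%-89% to 81%-94% at an assumed 0.6 SD and correlations of 0.3 to 0.7. A one-third dilution would arise only if an arm effect averaged over all three times were tested.

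The primary endpoint and the sample size are unaffected. The change is worth making because these sentences would otherwise carry over into the analysis plan.

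**What to change.** In the section *Analysis method and strategy*:

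1. For ANI, heart rate, blood pressure, FetCO2 and Pmax, model the +5 and +20 min readings as outcomes with the -5 min reading as covariate. Do not test the -5 min reading between arms; show it descriptively.
2. For pain, replace the per-time fallback with one Mann-Whitney test on each patient's time-weighted mean VAS from H0 to H2, and show the values at each time descriptively.

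The cost is a change of wording, since all the data are already to be collected. The timing detail for pain becomes descriptive, and the summary needs a short rule for missing VAS readings. One caution: randomisation comes before induction, so the -5 min reading is taken after allocation. Its use as a covariate rests on induction being the same in both arms, as the protocol plans.
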